### **9.2. Randomisation and Data Analysis**

Randomisation will occur after initial pre-treatment evaluation by an external and independent person who holds a secret randomisation list produced by Manchester University. This list will be stratified for severity of depression (high/low) and gender (males/females). Scores on pre-treatment HDRS will be used to form four groups: 1) high severity ( $\text{HDRS} \geq 20$ ), 2) low severity ( $\text{HDRS} \leq 19$ ), 3) males and 4) females. Participants will be assigned to the two therapists (PC and SF) based on therapist availability.

A statistical Analysis Plan will be drawn up before study completion and the final data will be analysed by independent trial statisticians at The University of Manchester department of bio-statistics.

## **10. Blinding**

All assessments will be administered by an independent assessor: [name] (CKA) CKA is a clinical psychologist with over 10 years of experience in therapy and assessment. This is a blinded study and all patients will be instructed not to reveal which treatment they have received at post-assessment and follow-up. In order to control for evaluation biases the independent assessor CKA will be asked to guess which treatment the patient has received at post-treatment assessment.

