## **1. Lay Summary**

Major Depressive Disorder (MDD) is one of the largest health problems worldwide. Psychological treatments show variable outcome rates with approximately 50% recovery in 'gold standard' cognitive behaviour therapies (CBT's). More effective treatments for depression are needed. Metacognitive therapy (MCT) is a newer treatment for MDD that has produced promising results in preliminary studies. Hagen et al (submitted) showed very large effect sizes in a randomised trial comparing wait-list with MCT. In their study 70-80% could be classified as recovered. The next step is to compare MCT with CBT in a definitive trial.

In this study a large parallel randomised single-blind trial will be conducted comparing metacognitive therapy (MCT) and Cognitive Behavioural Therapy (CBT). Adult patients diagnosed with major depressive disorder (MDD) will be assigned to treatment consisting of up to 24 sessions of either CBT or MCT and the treatment terminated when remission is reached defined as two consecutive scores of  $\leq 8$  on Beck's Depression Inventory II (BDI-II). Patients will be followed-up for 6 months post-treatment.

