Hagen et al (submitted) conducted a RCT comparing MCT to a wait-list condition. Results from this trial demonstrated very large effect sizes for MCT. In this trial thirty-nine patients were randomly assigned to immediate MCT (10 sessions) or to a 10-week wait list period (WL). The WL-group received 10 sessions of MCT after the waiting period. Participants receiving MCT improved significantly more than the WL group with very large controlled effect sizes for both depressive ( $d = 2.51$ ) and anxious symptoms ( $d = 1.92$ ). Approximately 70-80% could be classified as recovered on the BDI-II at post-treatment and 6 months follow-up following immediate MCT, whilst 5% of the WL patients recovered during the waiting period. These findings suggest that a non-hybrid, pure version of MCT may be particularly effective.

The current proposed trial is designed to test MCT for MDD by comparing it to a bona fide benchmark treatment; CBT. The trial utilises a strict methodology intended to reduce potential biases encountered in earlier studies. Patients are allocated to a total possible number of treatment sessions with pre-set criteria for potential early termination. They receive up to 24 sessions of therapy or until they reach a predetermined agreed recovered state. Strict session-by-session manuals for both treatments, expert supervision in both CBT and MCT and objective definitions of recovery and relapse will be adopted using a conservative and clinical change index as defined by Jacobson and Truax (1991).

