## **6. Outcome measures**

A battery of assessments will be administered by an independent assessor blind to treatment allocation at pre-treatment, post-treatment and at 6- months follow-up. The primary outcome measures are Beck's Depression Inventory (BDI-II) and the Hamilton Depression Rating Scale (HDRS). We chose both a self-rating scale and an interview-based scale in order to account for effects in different ways. In addition, several secondary self-report measures will be administered at pre-treatment, post-treatment and follow-up. The schedule of measures is presented in appendix 2:

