## **8. Safety Reporting and Adverse events**

An adverse event can be defined as:

*Any unfavourable, unintended effect that occurs during a study (e.g. symptom, diagnosis, test finding), having been absent at baseline, or if present at baseline appears to worsen.*

Information related to an adverse event will be captured in the case file and will be regularly monitored by the research management group in line with Good Clinical Practice Guidelines. In the case of adverse events like suicide attempts or sudden accidents it was decided to take action and report and exclude patients from the trial in order to get them hospitalised. However, no adverse events were reported in this trial.

A serious adverse event (SAE), is any untoward medical occurrence that

- results in death
- is life threatening (including suicide attempts)
- requires hospitalisation
- results in persistent or significant disability/incapacity

SAE's will be reported to the ethical committee that gave a favourable opinion to the study where in the opinion of the chief investigators the event was related to the research procedures. The response to SAE's will be determined on a case by case basis and will be in line with local policies and procedures.

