## **9. Trial design and analysis**

The trial is a single blind randomised, parallel between-groups design with 6-months follow-up (See trial flow diagram and timeline [Trial Registration Number: ISRCTN82799488 - Meta-cognitive Therapy (MCT) versus Cognitive Behaviour Therapy (CBT) for Depression. An assessor will undertake HRSD ratings and will remain blind to treatment allocation. Randomisation lists will be drawn up independently and held outside of the study team.

Severity of depression and gender of participants will be used as stratification variables during randomization. Participants will be assigned to therapists within treatment modality based on therapist availability.

Patients will be allocated up to a maximum of 24 sessions of MCT or CBT and assessed at pre-treatment, mid-treatment, post-treatment and at 6-months follow-up.

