### **9.1. Sample size**

There are currently no direct comparisons of MCT against CBT for depression to inform sample size estimates. Therefore we plan the current study to detect a post-treatment difference between groups based on mean BDI-II scores observed in previous studies that tested MCT or CBT separately (Dimidjian, Hollon, Dobson et al, 2006; Papageorgiou & Wells, 2015). The mean following MCT was 10 and the mean for CBT 14, suggesting a group difference of 4 points (a standardized effect size of 0.57), we used 7 as the standard deviation (Papageorgiou & Wells, 2015). Using an alpha of 5% and 90% power, this indicated that 64 participants per group were required (total n=128). We plan to increase the target sample by a further 20% to allow for pre-to-post treatment attrition.

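### The HDRS rater can infer BDI-II remission from an early end of treatment or from the BDI-II itself, while the section 10 safeguards conceal only which therapy was given

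*Protocol*

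**What the plan says.** **End of treatment.** The Lay Summary has "the treatment terminated when remission is reached defined as two consecutive scores of" 8 or below on the BDI-II. Section 2 puts it as "They receive up to 24 sessions of therapy or until they reach a predetermined agreed recovered state". Appendix 2 lists the BDI-II as sessional as well as at T1, T2 and T3. The HDRS is listed only at T1, T2 and T3.

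**Timing of assessments.** Section 9 has patients "assessed at pre-treatment, mid-treatment, post-treatment and at 6-months follow-up". The readable text ties the second HDRS rating to the end of treatment and gives it no calendar week.

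**Who assesses.** Section 10 states: "All assessments will be administered by an independent assessor". Section 6 likewise gives the assessment battery to a blind independent assessor at pre-treatment, post-treatment and follow-up, and it names both the BDI-II and the HDRS as primary outcomes.

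**What is concealed.** Sections 6 and 9 define blindness as blindness to allocation. In section 10, "all patients will be instructed not to reveal which treatment they have received at post-assessment and follow-up". The assessor also guesses the therapy, at post-treatment only.

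**Why there are two primary scales.** Section 6 explains: "We chose both a self-rating scale and an interview-based scale in order to account for effects in different ways".

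**The concern.** The length of treatment depends on one primary outcome, and the rater of the other primary outcome can observe that length. The assessor met the patient at T1. When the patient returns for T2 sooner than a full course would take, or mentions having finished early, remission on the BDI-II is a likely explanation. There is also a more direct route: the same person administers the BDI-II and may see its score before or during the HDRS rating. Nothing in section 10 closes either route, because the instruction to patients concerns only the name of the therapy.

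At stake is what the HDRS adds. It is the only interviewer-rated primary outcome. Patients know which therapy they receive, so their BDI-II answers can contain an expectancy effect. If the rater's score is influenced by knowing about BDI-II remission, part of any such effect passes into the HDRS. Agreement between the two scales would then look like independent confirmation when it is partly shared information. The guess check would not show this: a rater who correctly infers remission but guesses the therapy no better than chance would pass it.

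**Working it through.** **Step 1. What the rater could learn, set against what is concealed.**
- Therapy received: concealed by the patient instruction and tested by the guess.
- Number of sessions, end date and reason for ending: not mentioned in section 10.
- Sessional BDI-II scores: not mentioned in section 10.
- T2 and T3 BDI-II score: given by the same assessor, with no order of forms stated.

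**Step 2. How strong the timing signal is.** A treatment that ends early may reflect remission. It may also reflect dropout, for which section 9.1 makes an allowance ("We plan to increase the target sample by a further 20% to allow for pre-to-post treatment attrition"), or the step in section 8 to "report and exclude patients from the trial in order to get them hospitalised", although such patients may have no T2 visit. Session frequency is not stated, so elapsed time does not convert exactly into a session count. Timing is thus evidence of remission, not proof.

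**Step 3. The planning values.** Section 9.1 uses post-treatment BDI-II means of 10 (MCT) and 14 (CBT), SD 7, alpha 5% (two-sided assumed) and 90% power. The normal formula gives n per group = 2 × (1.960 + 1.282)² × 7² / 4² = 2 × 10.51 × 3.0625 = 64.4, that is 65 when rounded up, against 64 stated. The plan's figure is reproduced to within rounding. The present point does not depend on it.

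**Step 4. Illustrative size.** Let b be the number of HDRS points by which the rater scores a patient lower because remission is inferred, and let p be the share of each arm for whom it is inferred. The bias in the arm difference is b × (p_MCT − p_CBT). The Protocol gives neither b nor p. Take b = 1 to 3 as an assumption, and two stand-ins for p.

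- *Recovery rates quoted in the Lay Summary:* 70–80% for MCT and about 50% for CBT. The gap is 0.20 to 0.30, so the bias is 1 × 0.20 = 0.2 up to 3 × 0.30 = 0.9 HDRS points.
- *Share at 8 or below under the planning values, assuming normality:*
  - MCT: Φ((8 − 10)/7) = 0.388, or Φ((8.5 − 10)/7) = 0.415 with a half-point correction for whole-number scores.
  - CBT: Φ((8 − 14)/7) = 0.196, or Φ((8.5 − 14)/7) = 0.216.
  - The gap is 0.192 to 0.199, so the bias is 1 × 0.192 = 0.2 up to 3 × 0.199 = 0.6 HDRS points.
- *Equal rates and timing in the two arms:* the gap is 0, so the bias is 0 for any b.

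Neither stand-in is an early-finish rate. A patient who reaches two low scores near session 24, or scores 8 or below only once, gives no signal through timing.

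**The case against.** The strongest reply is that the Protocol promises blindness to allocation, not to clinical course, and keeps that promise on paper. Remission does not reveal the therapy. The HDRS interview elicits depressive symptoms directly, so the rater learns the patient's condition anyway; only the extra influence of knowing that treatment ended early, or of seeing the BDI-II, could do harm. That extra influence is not quantified, and no HDRS standard deviation is given against which to judge it. The reason given for using two scales is to view effects in different ways, which is not a promise that they are independent. Finally, section 9 refers to a flow diagram and timeline, and the flow chart in Appendix 1 was not readable here, so the timing of T2 for early finishers may be set there.

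Most of this stands, and it limits the point. Three stronger readings are tempting but unsupported:

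- *That an early visit discloses remission.* Dropout and exclusion after an adverse event are other routes out of treatment, and session frequency is not given. The visit can only suggest remission.
- *That the rater is unblinded to allocation.* Timing would hint at the arm only if the arms differ in speed of remission, and the guess check is aimed at that leak.
- *That the leak manufactures an arm difference.* With equal remission rates and timing the bias is zero. It can carry over a BDI-II difference, but it does not create one alone.

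What the reply leaves untouched is that section 10 conceals nothing about the course of treatment and does not separate the BDI-II from the HDRS rating. The second gap exists whatever the timing of T2.

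**Conclusion.** The point holds as a cheap improvement, not as a flaw that invalidates the HDRS result. Early ending on BDI-II remission, combined with one assessor who administers both primary scales before and after treatment, allows BDI-II information to reach the HDRS rater. The existing instruction and check do not address this. The consequence is that a BDI-II difference, including any expectancy component, can pass into the HDRS, so that the two primary outcomes corroborate each other less than they appear to.

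The size cannot be derived from the Protocol. The range of 0.2 to 0.9 HDRS points rests on two assumptions: a 1 to 3 point rater effect, which has no source in the document, and recovery rates from other studies used in place of early-finish rates. It should be read as an order of magnitude under those assumptions, with zero as the value when the arms remit equally often and equally early.

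**What to change.** In section 10:

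1. Extend the instruction to patients so that, besides the therapy received, they do not tell the assessor how many sessions they had, when treatment ended or why.
2. Require the HDRS to be completed and locked before the T2 or T3 BDI-II is seen, and keep sessional BDI-II scores, session count and reason for ending from the assessor.

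The cost is a reworded instruction sheet, a fixed order of forms and a restriction on what is passed to the assessor. No extra staff are needed. Masking will remain imperfect, because the same assessor saw the patient at T1 and may recall the date and the earlier severity. The clinical stopping rule is not affected. These steps belong in the blinding section because an analysis cannot remove what the rater already knew when scoring.

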## **11. Interventions**

In this study, protocols for CBT and MCT for MDD will be compared. These treatment manuals include the following elements:

### **11.1. Cognitive behaviour Therapy (CBT)**

The CBT group receive treatment using Beck's traditional cognitive therapy (A. T. Beck, Rush, A.J., Shaw, B. F., & Emery, G. , 1979 ) facilitated by Melanie Fennel's depression protocol from (*Cognitive behaviour therapy for psychiatric problems : a practical guide / Keith Hawton ... [et al.]*, 1989).

- an agreed 'problem-goal'-list
- 4-page booklet called "Coping with depression"
- negative automatic thought restructuring
- schema-related restructuring
- activity scheduling planned throughout treatment and level of mastery and pleasure increased
- relapse prevention

### **11.2. Meta-cognitive therapy for depression (MCT)**

Meta-cognitive Therapy will follow the Wells, (2009b) manual and consists of:

- practise of Attention Training
- detached mindfulness practise
- challenging negative metacognitive beliefs
- challenging positive metacognitive beliefs
- relapse prevention

## **12. Competency and treatment adherence**

In order to establish a fair and even level of competency and experience in CBT and MCT 24 patients were initially recruited to a pilot study (n=12 CBT, n=12 MCT) as training cases and not entered into the trial.

Treatment adherence and competency in both treatments is of vital importance. Highly experienced clinical psychologists PC and SF will deliver therapy. PC and SF have undergone specialist training and supervision in CBT with a minimum of ten years of clinical experience in the field. Leading senior psychologist and CBT therapist [name], with 35 years of CBT experience, will supervise the CBT condition and [name], the originator of MCT, will supervise the MCT treatment to ensure both treatments are delivered optimally and according to protocol.

All sessions will be recorded on videotape and screened by external psychologists [name] (SFN) and [name] (AL) for potential contamination of methods. Contamination is defined by the extent of ‘object-level’ work done in the MCT condition or ‘meta-level’ work done in the CBT condition..

20 random videotaped sessions (10 MCT and 10 CBT) will be selected and rated by final-year postgraduate psychology students for treatment adherence using the treatment fidelity checklists for CBT and MCT. To add an extra layer of quality checking to the CBT arm 10% of CBT tapes will be transcribed, translated and sent to external experts for evaluation of competency.

## Appendix 1: Study Flow Chart

[figure not shown]

## Appendix 2: Schedule of Measurement

| Measure    | T1 Pre | Sessional | T2 Post | T3 FU |
|------------|--------|-----------|---------|-------|
| Primary:   |        |           |         |       |
| BDI-II     | X      | X         | X       | X     |
| HDRS       | X      |           | X       | X     |
|            |        |           |         |       |
| Secondary: |        |           |         |       |
| BAI        | X      |           | X       | X     |
| MCQ-30     | X      |           | X       | X     |
| PBRS       | X      |           | X       | X     |
| NBRS       | X      |           | X       | X     |
| RRS*       | X      |           | X       | X     |
| DAS        | X      |           | X       | X     |
| YSQ        | X      |           | X       | X     |
|            |        |           |         |       |

BDI-II: Beck Depression Inventory

HDRS: Hamilton Rating Scale for Depression

BAI: Beck Anxiety Inventory

MCQ-30: Metacognitions Questionnaire 30 Item

PBRS: Positive Beliefs about Rumination Scale

NBRS: Negative Beliefs about Rumination Scale

RRS\*: Ruminative Response Styles Questionnaire

DAS: Dysfunctional Attitudes Scale (A)

YSQ: Young's Schema Questionnaire

*\*Note: Due to a printing error the RRS measure was corrupted and therefore dropped from the study analysis.*
